**Fig 1 pone.0325254.g001:**
[figure not shown]
Flow chart of study protocol. Flow chart of study protocol. CONSORT 2010 FLOW DIAGRAM.

Our study followed the standard protocol items: recommendations for interventional trials (SPIRIT), which aims to improve clinical trial quality (S1 Checklist, SPIRIT 2013 Checklist) *.

The patients included will be evaluated at three time points: t1 (8–12 h post-cesarean) will use an evaluation form, International Physical Activity Questionnaire (IPAQ) application, pain intensity, pressure pain tolerance and threshold, functional capacity, and cardiorespiratory physiological variables evaluation; t2 (20–24 h post-cesarean) and t3 (44–48 h post-cesarean) will evaluate pain intensity, pressure pain tolerance and threshold, functional capacity, and cardiorespiratory physiological variables.

After t1 and t2, patients allocated to intervention groups will receive their respective protocol.

### Data collection

The Fig 2 details the assessments and outcome variables.

**Fig 2 pone.0325254.g002:**
[figure not shown]
Template of recommendations of enrollment, interventions, and assessments schedule. t1: assessment 1; t2: assessment 2; t3: assessment 3; IPAQ: International Physical Activity Questionnaire; SAP: systemic arterial pressure; HR: heart rate; RR: respiratory rate; OS: oxygen saturation; NPS: numerical pain rating scale; DA: digital algometer; FIMS: Functional Independence Measure Scale; 2MWT: two-min walk test; BORG: Borg scale of perceived exertion.

### Clinical evaluation form

The patients will respond to an evaluation form. This form was designed for specific use in this study and considers sociodemographic data (name, address, age, educational level, marital status, associated diseases, and history of coronavirus infection); obstetric data (gestational age, parity, labor, date of birth, and postpartum period); clinical data (level of physical activity, pain intensity, pressure pain tolerance and threshold, functional independence, walking distance covered in the 2MWT, and subjective perception of effort).

### International physical activity questionnaire (IPAQ)

The IPAQ will be used to assess the level of physical activity. This questionnaire was validated in Brazil and classifies the patients as very active, active, irregularly active, or sedentary. Those who do not perform physical activity for at least 10 min during the week will be considered sedentary [14].

### Cesarean incision pain

In assessments 1, 2, and 3, the NPS and digital algometer will assess pain in the cesarean incision region.

Pain intensity will be assessed using the NPS [9,15]. This scale allows the patient to classify pain from level 0 (no pain) to level 10 (extreme pain). The evaluation of pain will follow verbal descriptors (0 = no pain; 1–3 = mild pain; 4–6 = moderate pain; and 7–10 = extreme pain). Pain in the abdominal region will be assessed with the patient at rest and in movement (one minute after the 2MWT).

Pressure pain tolerance and threshold will be assessed by a digital force gage algometer (WAGNER FDM model), a device with a 1 cm^2^ rubber disc connected to a pressure gauge, which displays values in kgf/cm^2^ [9]. The patient will be instructed to say “started” when the pressure applied by the device begins to evoke pain (threshold), and the pressure will continue until the patient says “stop” (tolerance). The pressure will be applied perpendicularly at the midpoint between the navel and the cesarian incision, taking the linea alba as a reference. The rubber disc will be covered with plastic film and cleaned with 70% alcohol before each patient.

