### Objectives

#### Primary objective.

This study aims to analyze the effect of TENS combined with LLLT photobiomodulation on pain outcomes in women after cesarean section.

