## Materials and methods

This randomized controlled clinical trial will be conducted at Divino Amor Maternity Hospital (Rio Grande do Norte, Brazil), and patients will be recruited according to the convenience of admission for cesarean birth and distributed into one of the 4 study groups (TENS alone, TENS combined photobiomodulation LLLT, Placebo or Control). This Study, the recruitment started in the July 2023 and not has been completed, the estimate to data collection be completed is august 2025, and results are expected decision-makers in resource allocation for improved care for this population, aiming to obtain insights into the most effective recuperation in postpartum.

To sample calculation, the study sample was the result of a probabilistic sampling process. For each group, the sample number was 17 volunteers, adding 20% of sample losses, the final number for each group was 22 volunteers. Thus, the sample size was 88 participants, based on the degree of pain in the surgical incision region (according to the numeric pain scale [NPS], graded from 0 to 10, and a reduction of 2 points in the pain score) and variable standard deviation for each group of 1.5. The alpha error was 0.05, the test power was 80% [9,13].

Eligibility criteria will encompass women within 8–12 hours post-cesarean birth; only woman habitual risk pregnancy; presence of pain NPS ≥ 3 in the cesarean incision region; no clinical or obstetric complications; no infectious process; undergoing drug treatment (anti-inflammatories, analgesics, and anti-gas drugs) with the same intake interval; absence of neurological or musculoskeletal disorders or alterations; and not physically active.

Exclusion criteria will encompass discontinuation of TENS or the LLLT photobiomodulation interventions; failure to perform the 2-min walk test (2MWT) during the assessment period; presence of clinical or obstetric instability during the assessment period; or patients who have already undergone TENS intervention or have a cognitive deficit.

The sample will be randomized (www.randomization.com) in four groups: TENS intervention combined with LLLT photobiomodulation, TENS alone, placebo, and control. The groups will be coded, and allocation will be done in sealed and opaque envelopes, numbered consecutively.

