### Statistical analysis

Data analysis will be performed using SPSS software version 22.0 (IBM Corp. USA), and in all statistical analyses, p values < 0.05 were considered as statistically significant. Will be performed Shapiro-Wilk test and Levene for normality of the data distribution and equality of variances. Descriptive statistics will be presented using the measures of central tendency. Mauchly’s test of sphericity will be used to validate the correlation of the repeated measures, and if the assumption of sphericity was violated, the Greenhouse-Geisser correction will be applied. Two-way repeated measures ANOVA will be to compare the effects of TENS combined with LLLT photobiomodulation between groups (TENS alone, Placebo and Control) over time (assessment t1, t2 and t3) on a primary outcome (pain) and secondary outcomes (functional capacity, systemic arterial pressure, respiratory and heart rates, oxygen saturation and Functional Independence Measure). When appropriate, post hoc comparisons will be carried out using Tukey’s post hoc correction for multiple comparisons. The effect size will be calculated by Cohen’s. For the missing data, intention to treat analysis will be used.

For better data management and quality control the investigator responsible for randomization will be responsible for organization the collected patients information in spreadsheets and ensure confidentiality without personal identification of the research participants.

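### The primary outcome, pain, covers four measures each judged at 0.05, so the chance of a false-positive group difference on it is about 10% to 19%; no primary contrast is named

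*Protocol article*

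**What the plan says.** The primary objective is to study the combined therapy's effect "on pain outcomes in women after cesarean section", in the plural, with no instrument, time point or comparator. The Statistical analysis section plans a two-way repeated measures ANOVA over t1, t2 and t3 "on a primary outcome (pain) and secondary outcomes". The secondary outcomes it then lists are functional capacity, arterial pressure, respiratory and heart rates, oxygen saturation and functional independence. No pain measure is among them.

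The section Cesarean incision pain says: "In assessments 1, 2, and 3, the NPS and digital algometer will assess pain in the cesarean incision region". The NPS is taken twice: "Pain in the abdominal region will be assessed with the patient at rest and in movement (one minute after the 2MWT". The algometer also gives two readings: "Pressure pain tolerance and threshold will be assessed by a digital force gage algometer". That makes four measures.

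On error control, the Statistical analysis section says that "in all statistical analyses, p values < 0.05 were considered as statistically significant", and it uses "Tukey’s post hoc correction for multiple comparisons" for post hoc comparisons. It gives no rule across measures.

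The sample size in Materials and methods is "based on the degree of pain in the surgical incision region (according to the numeric pain scale [NPS". It uses a 2-point reduction, SD 1.5, alpha 0.05 and 80% power, and does not say rest or movement, which time point or which pair of groups. The abstract sets the comparison as combined therapy against TENS alone. The Statistical analysis section compares the combined arm with TENS alone, placebo and control.

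**The concern.** The four measures are not interchangeable. The NPS is self-rated intensity, at rest or after a walk test. The algometer records pressure in kgf/cm² at a point midway between navel and incision. They can disagree, and the article does not say how a mixed result would be read. If each has its own 5% chance of a false-positive group difference, the chance that at least one shows such a difference is well above 5%. A report of an effect on the primary outcome would then carry weaker evidence than the stated alpha suggests.

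The second issue concerns power, not error. With no named contrast, the comparison in the abstract goes through a correction over all six group pairs, three of which do not involve the combined arm.

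**Working it through.** **Inputs from the article.** Four groups; 17 evaluable per group, 22 after losses; difference 2 NPS points; SD 1.5; alpha 0.05; four pain measures; Tukey within each analysis.

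**Assumptions, not in the article.** Tests are two-sided. The correlation among the four measures is taken from 0 to 0.9. Each measure is represented by one between-group analysis, which simplifies the repeated measures model.

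**The plan's own figures.** The losses step reproduces: 17/(1 − 0.20) = 21.25, rounded up to 22, and 4 × 22 = 88. The 17 does not follow from the stated inputs: a two-sample t-test needs 10 per group and a Tukey-corrected pair needs 14. The trial is thus larger than its inputs require. This is a separate matter and does not affect the point here.

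**Error rate across measures.** For four independent measures at 0.05 each, 1 − 0.95⁴ = 0.185; for two, 1 − 0.95² = 0.0975. Simulating four groups of 22 with no true differences and Tukey applied within each measure gives the chance of at least one false pairwise difference:

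| Correlation | Four measures | Two NPS measures |
|---|---|---|
| 0 | 19.0% | 9.8% |
| 0.3 | 17.4% | 9.5% |
| 0.5 | 16.0% | 9.3% |
| 0.7 | 13.9% | 8.5% |
| 0.9 | 9.8% | 7.2% |

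The four-measure column uses 20,000 runs per row and the two-measure column 40,000.

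**Contribution of the six pairs.** For one measure, the simulated rate over all six Tukey-corrected pairs is 4.8% to 5.3%. The excess comes from the number of measures alone.

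**One contrast under Tukey.** With 4 × (17 − 1) = 64 degrees of freedom, the Tukey critical value on the t scale is 2.64, a two-sided error of 1.05% for a single pair. Over four independent measures, 1 − (1 − 0.0105)⁴ = 4.1%; simulation (22 per group) gives 2.2% at correlation 0.9. So the error for combined versus TENS alone by itself stays below 5%.

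**Power for one pair.** The standard error of a difference is 1.5 × √(2/17) = 0.514, so 2 points corresponds to a noncentrality of 2/0.514 = 3.89. The critical value is 2.64 under Tukey and 2.00 for one planned contrast.

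| True difference | Tukey, 17 per group | One planned contrast, 17 per group |
|---|---|---|
| 2 points (protocol) | 89% | 97% |
| 1.5 points (assumed) | 61% | 82% |
| 1 point (assumed) | 25% | 48% |

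The difference detectable with 80% power is 1.80 points under Tukey and 1.46 for one planned contrast. With 22 per group these become 1.57 and 1.28, and power for 2 points is 96% and 99%.

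**Check of the remedies.** One measure with one contrast gives 5% by construction. Tukey at 0.05/4 on each of four measures gives a simulated overall rate of 2.8% to 5.0%. Power per pair for a standardised effect of 2/1.5 is then 76% at 17 and 90% at 22 per group; 80% needs 19 evaluable per group. This assumes that every measure has the standardised effect planned for the NPS.

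**The case against.** The best defence is that the NPS is the intended primary measure. The trial is sized on it, eligibility uses it, and the article elsewhere lists pressure threshold and tolerance apart from pain intensity. This has weight and is why the narrower figure of 7% to 10% is given. It does not settle the matter: the article says both instruments assess incision pain, lists neither as secondary, and leaves rest versus movement and the time point open.

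It is also fair to say that no success rule is written down. A reader might infer that any one significant measure would count as success. The article does not say so; it only leaves that open.

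Four stronger readings are tempting and are not supported:

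- *That testing six pairs inflates the error.* Tukey is prescribed and holds each measure near 5%.
- *That the combined versus TENS alone contrast itself carries a 13% to 18.5% error over four measures.* That would need unadjusted tests. Under Tukey it is about 2% to 4%.
- *That t2 and t3 double the tests to eight, with an error of 19% to 33%.* The plan is one repeated measures ANOVA per outcome, not separate unadjusted tests at each time.
- *That the trial is underpowered for its main contrast.* At the protocol's own 2 points and SD 1.5, power under Tukey is 89%, above the planned 80%. The article gives no smaller figure for that contrast.

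Nor are the other pairs idle comparisons: placebo and control are named comparators in the Statistical analysis section.

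**Conclusion.** The concern holds for the number of primary measures. As written, the plan gives about a 10% to 19% chance of at least one false-positive group difference on pain, or about 7% to 10% if only the two NPS scores are primary, against the single 5% in the sample size. The range depends on an assumed correlation of 0.9 to 0 and on one between-group analysis per measure.

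The missing primary contrast is a lesser, separate weakness. It costs 8 percentage points of power at the protocol's 2 points (97% − 89%). The cost is larger only if the two active arms differ by less, which is an assumption here. The point deserves correction before analysis but does not undermine the design.

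**What to change.** Before analysis, by a dated amendment, name one primary test: one NPS measure (for example at rest), at one time point (for example t3, after both sessions), for one contrast (combined versus TENS alone, two-sided 0.05). Make the other NPS score, threshold, tolerance, the other time point and the other pairs secondary, with Tukey kept for those pairs. Rest and t3 are proposals; the article does not dictate either.

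Alternatively, keep all four measures primary and apply Tukey at 0.05/4 to each.

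The first option costs the sponsor the right to call the other pain measures primary. The second lowers power per pair to 76% if only 17 per group are evaluable. Recruitment began in July 2023, so either is a mid-trial change that must be documented.

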### Functional independence measure (FIM)

This study will evaluate the functional independence of the patient in the TENS combined with LLLT photobiomodulation group. The FIM is an instrument validated for the Portuguese language and classifies patients according to their ability to perform an independent activity, quantifying their need for assistance [15].

### Functional capacity (2MWT)

The 2MWT will assess the distance (meters) covered during 2 min of walking and will be used for measuring functional capacity [16]. The patient will be asked to walk for 2 min in a 30-m corridor, with the time recorded with a digital stopwatch and distances delimited with tape on the floor. Patients will be encouraged to walk as fast as possible without running, respecting their limits. The examiner will stay half a meter behind the patient to ensure safety. Two practical attempts will be performed, and the 2MWT with the longest distance will be recorded in the assessment. A 30-minute break between the two attempts will be given for the patients to rest [16,17]. Cardiorespiratory variables will be monitored before and immediately after the 2MWT, as well as the self-reported perception of effort.

### Subjective perception of effort

Patients will be asked about their subjective perception of respiratory effort before and during the 2MWT using the Borg scale of perceived exertion [18]. This scale is graded from 6 (no exertion at all) to 20 (maximal exertion). Higher values correspond to a greater sensation of dyspnea.

### Blood pressure, heart and respiratory rates, and oxygen saturation

Physiological cardiorespiratory variables, such as blood pressure, heart and respiratory rates, and oxygen saturation, will be evaluated at t1. In t2 and t3, this evaluation will be performed before, during, and after the 2MWT.

### Intervention protocols

Protocol for TENS combined with LLLT photobiomodulation: Both interventions will be applied simultaneously, with the patient positioned in the supine position and a neutral posture. We will follow a TENS intervention protocol previously described [1], consisting of low-intensity TENS (30 min, 100 Hz, and 75 µs) applied using two channels and four electrodes (size 5 x 3 cm) placed in the skin surface with conductive gel above and below the cesarean incision, sanitized with 70% alcohol. The LLLT photobiomodulation intervention protocol will follow a reference from the literature [9], consisting of 660 nm (red), energy of 2 J per point, and power of 100 mW, performed in two sessions without skin contact in the cesarean incision. The LLLT intervention will be punctual and applied perpendicularly to the skin surface in the line of the cesarean incision [8]. The number of points applied will depend on the extent of the cesarean incision. The time per point will be 20 seconds, and the distance of 1 cm between application points will be respected. To perform the application with LLLT photobiomodulation, the application pen will be cleaned with 70% alcohol before each patient. Asepsis in the cesarean incision region will also be performed using 70% alcohol before and after the intervention. Only the therapist and the patient will be present during this application due to the need for specific protective glasses for the LLLT. The Fig 3 represent the procedure to application TENS combined with LLLT photobiomodulation.

**Fig 3 pone.0325254.g003:**
[figure not shown]
TENS combined with LLLT photobiomodulation. a: cesarean incision; b: TENS channel 1; c: TENS channel 2; d: LLLT photobiomodulation; e: electrode (size 5 x 3 cm).

Protocol for TENS alone: patients will receive the same TENS intervention parameters and positioning previously described in the TENS combined with LLLT photobiomodulation protocol.

Protocol for the placebo: Patients will follow the same TENS combined with LLLT photobiomodulation protocol as in the intervention group, but the equipment will not emit light or electric current.

Protocol for the control: Patients will only undergo t1, t2, and t3.

### Statistical analysis

Data analysis will be performed using SPSS software version 22.0 (IBM Corp. USA), and in all statistical analyses, p values < 0.05 were considered as statistically significant. Will be performed Shapiro-Wilk test and Levene for normality of the data distribution and equality of variances. Descriptive statistics will be presented using the measures of central tendency. Mauchly’s test of sphericity will be used to validate the correlation of the repeated measures, and if the assumption of sphericity was violated, the Greenhouse-Geisser correction will be applied. Two-way repeated measures ANOVA will be to compare the effects of TENS combined with LLLT photobiomodulation between groups (TENS alone, Placebo and Control) over time (assessment t1, t2 and t3) on a primary outcome (pain) and secondary outcomes (functional capacity, systemic arterial pressure, respiratory and heart rates, oxygen saturation and Functional Independence Measure). When appropriate, post hoc comparisons will be carried out using Tukey’s post hoc correction for multiple comparisons. The effect size will be calculated by Cohen’s. For the missing data, intention to treat analysis will be used.

For better data management and quality control the investigator responsible for randomization will be responsible for organization the collected patients information in spreadsheets and ensure confidentiality without personal identification of the research participants.

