**Methods:**

This is a protocol of a randomized clinical trial that will be conducted at Divino Amor Maternity Hospital (Rio Grande do Norte, Brazil). A total of 88 patients undergoing cesarean section will be distributed in four groups: TENS combined with LLLT photobiomodulation, TENS alone, placebo, and control. The patients included in the study will be evaluated at three time-points: assessment 1 (8–12 hours postpartum), assessment 2 (20–24 hours postpartum), and assessment 3 (44–48 hours postpartum). Data will encompass sociodemographic and clinical information, pain assessment, functional performance, and cardiorespiratory physiological variables (systemic arterial pressure, heart and respiratory rates, and oxygen saturation). The combined intervention group will follow the protocol of two sessions with low-intensity TENS (30 min, 100 Hz, and 75 µs), with electrodes above and below the cesarean incision, and LLLT photobiomodulation (660 nm, 2 J per point, and 100 mW), without touching the cesarean incision. The TENS alone group will follow the same low-intensity TENS protocol used in the combined intervention. Interventions (combined and isolated) will be delivered after completion of assessments 1 and 2.

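### Pre-treatment t1 pain is entered as an outcome level with no adjustment for it; if groups are compared on means over t1 to t3, a constant effect shrinks by one third

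*Protocol article*

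**What the plan says.** Pain is the primary outcome. The Statistical analysis section plans a group-by-time repeated measures ANOVA, in which "Two-way repeated measures ANOVA will be to compare the effects of TENS combined with LLLT photobiomodulation between groups", and the time factor runs "over time (assessment t1, t2 and t3". Sphericity is checked with Mauchly's test, with the Greenhouse-Geisser correction if it fails. Where judged appropriate, "post hoc comparisons will be carried out using Tukey’s post hoc correction for multiple comparisons". Neither the factor nor the time point for the Tukey step is named, and no baseline adjustment is mentioned. The software is SPSS 22.

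On timing, the abstract states "Interventions (combined and isolated) will be delivered after completion of assessments 1 and 2", and the text after Fig 1 agrees: "After t1 and t2, patients allocated to intervention groups will receive their respective protocol". Both place t1 before any treatment.

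The sample size paragraph in Materials and methods uses "a reduction of 2 points in the pain score", SD 1.5 in each group, alpha 0.05 and 80% power. It gives 17 per group, raised to 22 for losses.

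**The concern.** No treatment effect can exist at t1. Once t1 is one of three outcome levels, any comparison of groups averaged over time mixes one null assessment with two treated ones. The estimated difference is pulled towards zero, and chance differences in t1 pain enter the comparison instead of being removed.

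This route is a realistic one. In the SPSS repeated-measures procedure, the Tukey post hoc option belongs to the between-subject factor, so it compares group means taken over all time levels. An analyst who followed the section literally could end there.

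The comparison most exposed is the one the abstract singles out, combined treatment against TENS alone. Both arms are active, so the difference may well be under 2 points, and lost power could then decide the result.

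**Working it through.** **Inputs from the article.** Effect 2 points, SD σ = 1.5, two-sided alpha 0.05 (sidedness assumed), four groups, n = 17 evaluable per group.

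**Assumptions.** The correlation ρ between assessments is not given, so 0.3, 0.5 and 0.7 are used, with equal variances and equal correlations at all three assessments. SD 1.5 at t1 is also assumed; the entry rule of pain at least 3 may narrow the spread at t1.

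**The plan's own figure.** 17/(1 − 0.20) = 21.25, rounded up to 22, and 4 × 22 = 88, so the inflation step reproduces. The 17 itself does not follow from the stated inputs by a two-group formula: 2 × (1.96 + 0.84)² × 1.5²/2² = 8.8, so 9. That is a separate matter. Here 17 is taken as the number analysed.

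**Step 1: effect on the averaged scale.**
- Constant effect (0, 2, 2): (0 + 2 + 2)/3 = 1.33, one third below 2.
- Effect that builds up (0, 1, 2): (0 + 1 + 2)/3 = 1.00. This is one third below the post-treatment mean of 1.50 and half the t3 effect.

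**Step 2: standard deviation for each analysis.**
- Mean over t1–t3: σ√((1 + 2ρ)/3) = 1.10, 1.22, 1.34 at ρ = 0.3, 0.5, 0.7.
- Mean of t2 and t3, adjusted for t1: σ√((1 + ρ)/2 − ρ²) = 1.12, 1.06, 0.90.
- Mean of t2 and t3 minus t1: σ√((1 + ρ)/2 + 1 − 2ρ) = 1.54, 1.30, 1.01.

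Worked at ρ = 0.5: averaged variance 2.25 × 2/3 = 1.50, SD 1.225, standardised effect 1.333/1.225 = 1.09. Adjusted variance 1.6875 − 0.5625 = 1.125, SD 1.061, standardised effect 2/1.061 = 1.89.

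**Step 3: power.** For a pair of groups, the noncentral t has noncentrality (difference/SD) × √(17/2), and the Tukey critical value for four groups is about 2.64 (64 error df; 63 with the covariate). The small cost of estimating the covariate slope is otherwise ignored. The F tests use the noncentral F with one arm differing from the other three.

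| Constant effect at t2 and t3 | ρ = 0.3 | ρ = 0.5 | ρ = 0.7 |
|---|---|---|---|
| 2 points: Tukey, mean of t1–t3 | 82% | 70% | 60% |
| 2 points: group main-effect F | 96% | 90% | 84% |
| 2 points: group-by-time F (6 df) | 95% | 99% | about 100% |
| 2 points: Tukey, change from t1 | 87% | 97% | 99.9% |
| 2 points: Tukey, t1 as covariate | 99.4% | 99.7% | about 100% |
| 1.5 points: Tukey, mean of t1–t3 | 51% | 40% | 33% |
| 1.5 points: group-by-time F (6 df) | 72% | 87% | 99% |
| 1.5 points: Tukey, change from t1 | 58% | 76% | 95% |
| 1.5 points: Tukey, t1 as covariate | 89% | 93% | 98.5% |

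Tukey at a single unadjusted post-treatment assessment has 89% power at 2 points, whatever ρ is. For the build-up pattern (0, 1, 2), the averaged and covariate-adjusted Tukey rows equal their 1.5-point rows, because the averaged difference is again 1.00 and the post-treatment mean difference again 1.50.

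**Step 4: baseline imbalance.** The standard error of a t1 difference between two arms of 17 is 1.5 × √(2/17) = 0.51 points. An imbalance of that size shifts the expected difference in t1–t3 means by (1 + 2ρ)/3 of it: 0.27, 0.34 or 0.41 points.

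**The case against.** A reader might infer that the plan as written shrinks the treatment effect by one third. The article does not commit to that. In a group-by-time design the usual treatment test is the interaction, where t1 serves as the reference for change. Mauchly's test and Greenhouse-Geisser concern only within-subject effects (time and group-by-time), which suggests that those are the tests the authors have in mind. The Tukey step is conditional and names no factor; applied at t2 or t3 separately it would not include t1. The deciding contrast may also be fixed in a fuller document that is not shown, so its absence here cannot be the finding.

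A reader might also infer that the planned ANOVA is invalid or the trial underpowered. Neither follows. Under randomisation the interaction is a valid test, it is not biased by chance t1 imbalance in the way averaged means are, and at the planned 2 points its power is 95% or more.

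All of that stands and limits the point. What remains is that the section as stated makes t1 an outcome level, makes no adjustment for it, and pairs the model with a post hoc method whose direct route in the named software averages over t1. The interaction does not rescue the pairwise question: with 6 df over four groups it yields no estimate for combined versus TENS alone. At 1.5 points it also has less power than the adjusted pairwise contrast at ρ = 0.3 and 0.5, though about the same at 0.7.

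**Conclusion.** The concern holds conditionally. The one-third shrinkage (2.00 to 1.33 points) applies to the group main effect and to Tukey on means over t1–t3. For a constant 2-point effect, that Tukey comparison has about 60% to 82% power, against 99% or more with t1 as covariate. It does not apply to the group-by-time interaction or to comparisons made at t2 or t3.

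The case for using t1 as a covariate does not depend on the unfavourable reading. Adjustment also beats Tukey on change from t1, most clearly for a smaller effect and a weak correlation (89% against 58% at 1.5 points and ρ = 0.3). The exact figures rest on the assumed correlations, on SD 1.5 at every assessment including t1, and on 17 analysed per arm. The ordering of these Tukey comparisons is the same at every correlation tried. This is a free improvement to the primary analysis, not evidence that the planned one is wrong in principle.

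**What to change.** Replace the primary analysis wording along these lines: pain at t2 and t3 will be analysed in a mixed model for repeated measures with group, time, group-by-time and the t1 value as covariate, and an unstructured covariance. A longitudinal model with the t1 mean constrained equal across groups would serve equally well.

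State which post-treatment contrast decides (the t2–t3 mean, or a named assessment). Report adjusted differences with 95% CIs for combined versus TENS alone, versus placebo and versus control, and apply the multiplicity correction to these contrasts. Add that Tukey will not be applied to means that include t1.

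The cost is wording only. The t1 score is already collected, SPSS MIXED fits the model, and the sample size and visit schedule stay as they are. The change should be dated before the outcome data are analysed by group.
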